### Enhanced Usual Care

Participants randomized to the control group, receive monthly e-mails asking them to upload their pedometer data. Those data are stored but not used for any further feedback to patients. Although the pedometer is an enhancement to what patients receive in standard practice, past studies suggest that pedometers in isolation are unlikely to result in a sustained increase in walking among generally sedentary individuals [43]. While control group participants are provided with log-on information for the study website, their access is limited to completing study surveys and reporting adverse events.

### Pedometer-Based, Internet Mediated Intervention

The study intervention is based on the Stepping Up to Health program developed by Richardson and colleagues [63]. The intervention consists of three primary components (Figure 1). Active intervention participants receive weekly e-mail reminders to upload their pedometers, weekly individualized walking goals and full access to the study website. Specifically, each person in the intervention receives computer generated personal walking goals. The goals are sent to participants by e-mail on a weekly basis and are automatically adjusted to assist the individual with increasing his/her step count at a reasonable pace or help with countering negative thoughts and behaviors when a particular goal is not achieved. Besides receiving a new goal each week, participants receive graphical and written feedback about their progress toward their goals when they log into the study website (Figure 3). The graph shows a breakdown of steps by day, week and month, while the text informs the participant about their average step count for the week and how many days his or her goal has been met up until that day. For example, it might read, "You have met your walking goal on 3 of 7 days. Your average daily step count for the week is 3568." While the general intent is for the total step goals to increase over time and thus promote an increase in walking, because the goals are established based on the participant's own activity level the goals can also be lower from one week to the next. Resetting a goal at a lower level can be beneficial when trying to counter the potential negative reaction and sense of failure for participants who may not be achieving the higher goals or for participants who might need to be reminded to start low and go slow after a relapse or health event that may have led to a decreased step count in the prior period. Participants who are not uploading data weekly receive step goals based on the last time they uploaded and will have the same goal until new activity takes place.

**Figure 3 F3:**
[figure not shown]
**Screen shots of study website**. The screen shots show the login page, the graphical and text feedback provided to an intervention participant and a list of active e-community topics. The screen shots also show the tailoring by gender, with variations in color and the photos that are displayed.

The participant website is tailored according to gender and includes information and messages (e.g., motivation, time constraints) to promote walking and a healthy lifestyle. New motivational or informational messages addressing potential barriers to physical activity (e.g., weather) or issues related to diet or other health conditions (e.g., cardiovascular disease, diabetes) appear every other day. Brief updates about topics in the news or new research findings related to back pain or physical activity are generally posted on a weekly basis so the website content does not get stagnant. The website also includes the materials and hand-outs that participants received at back class as well as a video demonstrating the proper technique for the strengthening and stretching exercises taught during the class.

The e-community component of the intervention consists of a thread-based forum that allows participants to conduct asynchronous text-based discussions. Each participant selects a pseudonym in order to establish an on-line identity while maintaining privacy. Following work by Lorig et al. [18], the e-community is used to provide both peer and professional social support. The e-community allows intervention participants to post messages, which can include asking questions, making suggestions or sharing success stories. The messages are monitored by research staff, including a physical therapist who does not provide individual medical advice but can respond to questions or back pain related issues with general information based on the VA low back pain guidelines. The forum also serves as a venue for generating competitions among the intervention participants to encourage walking and meeting walking goals. An advantage of an electronic forum is that it can prevent e-mail overload and all postings can be monitored to prevent inappropriate messages or communication. Experience to date shows that inappropriate messages are rare.

### Monitoring and Reporting of Adverse Events

The study includes several mechanisms for monitoring, troubleshooting and identifying the minority of patients for whom a relatively low intensity walking program is considered unsafe. Medical clearance is required and patients for whom walking is not a recommended activity, due to for example balance problems or cognitive impairment, are not eligible to participate. However, since we are trying to use relatively few exclusion criteria it is possible that some patients will be eligible but later develop signs or symptoms that suggest walking may no longer be a safe activity. Both intervention and control participants are encouraged to report adverse events including any health problems they experience whether or not they are thought to be study related. Participants can report adverse events by using a link on the website, by e-mail and over the phone. All email messages contain a link to the adverse events reporting form and the study's toll-free number for reporting adverse events. After completing four weeks of the study and every eight weeks thereafter, participants are prompted to complete a survey on the website that asks about specific adverse events and symptoms. This information is closely monitored by project staff so that any patients who appear to be experiencing a potentially serious health-related problem can be contacted for further assessment and follow-up.

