### Description of Measures and Data Collection Procedures

Measures have been selected to assess our principal hypothesis that the proposed intervention will increase walking, as measured by step counts, among intervention patients relative to controls and reduce pain-related functional interference. Potential mediating factors, such as self-efficacy, and the benefits of a walking program, such as improvements in mood and quality of life, are also of significant interest. Data collection includes a computer-based survey completed at baseline, 6 months and 12 months, a six-minute walk test conducted at baseline and 12 months, and the step counts collected when participants upload their pedometer data. We are also collecting quantitative information about patients' use of the system via computerized records that the system maintains of all contacts. Health services use is assessed by patient report and by data obtained from the VA computerized medical record system.

The primary outcome for this study is pain-related disability and functional interference. Following the recommendations made through the Initiative on Methods, Measurement, and Pain Assessment in Clinical Trials (IMMPACT) [64], we are using both a disease-specific measure, the Roland and Morris Back Pain Disability Questionnaire (RDQ) index, and a generic measure of pain-related functioning from the medical outcomes study [65]. We hypothesize that the intervention will decrease back pain-related disability and pain-related functional interference. The RDQ index is a 24-item scale that has been widely used in back pain studies as a measure of self-perceived disability. The scale has good internal consistency, discriminative validity and is sensitive to change [66-69]. The medical outcomes study (MOS) pain measurement instrument assesses the effect of pain on mood and behaviors as well as the severity of pain over the past 4 weeks [65]. There is limited information about how the MOS instrument compares with other pain assessments but it is easily understood by patients and produces scales that have relatively good internal consistency [65].

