### Analysis Plan

The patient is the primary unit of analysis for this study. Our sample size calculation was based on the RDQ index as the primary endpoint with a minimally detectable effect size determined as a difference of 0.4 standard deviations (SD) based on published data [68,77,78]. To detect a difference of 0.4 SD with 80% power using a two-sided 0.05 level two-group t-test, we will enroll 130 subjects in each group, to allow for an attrition rate of 30% at one year and a sample with outcome data of 100 patients in each group.

To determine whether the intervention reduces pain-related functional interference we will compare the difference in the RDQ index at 12 months between the two groups using a linear mixed-effects model. Similarly, mixed-effects models will be used to assess the effect of the intervention on step counts, quality of life, pain intensity, pain related fear and self-efficacy for exercise. Identifying factors associated with a sustained increase in walking over a 12-month timeframe is an exploratory analysis within the intervention group.

In addition, to understand features of successful versus less successful intervention experiences, we will analyze data collected through our monitoring of participant system use and semi-structured interviews conducted with a purposeful sample of intervention participants (choosing a sample of eight who expressed high satisfaction with the intervention and/or improved walking and a sample of eight with poor satisfaction and/or outcomes). Using standard qualitative methods [79], we will identify central themes from these interviews associated with the success of the intervention.

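### Adverse events are found only through participant report, so serious events in those who disengage may be missed, although VA record data already obtained could serve as a second source

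*Protocol article*

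**What the plan says.** The section Monitoring and Reporting of Adverse Events describes two kinds of report.

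- Unprompted: "Participants can report adverse events by using a link on the website, by e-mail and over the phone". Study e-mails carry a link to the reporting form and a toll-free number.
- Prompted, at week 4 and then at eight-week intervals: "participants are prompted to complete a survey on the website that asks about specific adverse events and symptoms".

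Staff action then follows from what has been reported: "This information is closely monitored by project staff so that any patients who appear to be experiencing a potentially serious health-related problem can be contacted". Medical clearance is required before entry. The section also accepts that, because exclusions are deliberately few, walking may become unsafe for some participants after enrolment.

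Two other sections bear on the point. The Analysis Plan states that "we will enroll 130 subjects in each group", and gives the reason: "to allow for an attrition rate of 30% at one year and a sample with outcome data of 100 patients in each group". Description of Measures and Data Collection Procedures states: "Health services use is assessed by patient report and by data obtained from the VA computerized medical record system". The same section explains that staff can see whether a participant is uploading step counts. No adverse event inquiry is described as following from that.

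**The concern.** Every source of adverse events named after enrolment depends on the participant's continued engagement. Someone who has been admitted to hospital, has died, or has stopped because of a health problem may be less able to answer a website survey than someone who is doing well. If so, missing reports are not a random sample, and a count based on self-report alone would tend to be too low.

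Serious events are likely to be few in a trial of 260, so missing even several could change the picture given by arm. A source that does not depend on engagement is already coming into the study, but it is named for another purpose.

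**Working it through.** **1. Sources of adverse events, side by side**

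| Source described | Needs the participant to act? | Named as an adverse event source? |
|---|---|---|
| Website link, e-mail, telephone | Yes | Yes |
| Prompted website survey | Yes | Yes |
| Patient-reported health services use | Yes | No |
| VA medical record data | No | No (stated purpose: health services use) |
| Upload tracking by staff | No | No |

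The survey is prompted at week 4 and every 8 weeks after, that is at weeks 4, 12, 20, 28, 36, 44 and 52: seven occasions, each needing a response. The only listed source of clinical events that does not depend on engagement is the VA record.

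**2. Size of the group at issue**

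Inputs, all from the Analysis Plan: 0.4 SD difference, 80% power, two-sided 0.05 t-test, 100 per group with outcome data, 130 per group enrolled, 30% attrition.

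- The plan's own figure first. An exact two-group t-test calculation gives 99.1 per group, which agrees with the stated 100.
- Enrolment needed to keep 100 after 30% loss: 100 / (1 − 0.30) = 142.9, so 143. The stated 130 equals 100 × 1.30 instead.
- Loss implied by going from 130 to 100: 1 − 100/130 = 23.1%, or 30 per group and 60 in total.
- Loss at the stated 30%: 0.30 × 260 = 78 in total, or 39 per group.

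The article therefore supports a range of 60 to 78 of 260 without 12-month outcome data. The enrolment arithmetic matters here only because it sets the lower end of that range.

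**3. What this could mean in events**

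The article gives no serious event rate, so what follows is an assumption shown over a range. Let r be the annual risk and f the fraction of the year not covered by self-report. Expected participants with an event in the uncovered time = m × [1 − (1 − r)^f].

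| Assumed r | f | m = 60 | m = 78 |
|---|---|---|---|
| 2% | 0.5 | 0.6 | 0.8 |
| 2% | 1 | 1.2 | 1.6 |
| 5% | 0.5 | 1.5 | 2.0 |
| 5% | 1 | 3.0 | 3.9 |
| 10% | 0.5 | 3.1 | 4.0 |
| 10% | 1 | 6.0 | 7.8 |

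That is between about 0.6 and 7.8. For scale, the same annual risks in all 260 give 260 × 0.02 = 5.2 to 260 × 0.10 = 26. The table treats everyone without 12-month outcome data as unreported for the fraction f, which overstates the gap where people go on reporting. It also gives them the same risk as everyone else, which understates the gap if loss is related to harm.

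**The case against.** The strongest case against is that much of the concern can only be built from silence. This is a journal article that condenses a fuller protocol, and a safety plan may well cover non-responders and further event sources. Four stronger readings are tempting, and the document supports none of them.

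- A reader might infer that an unanswered survey leads to no action. The article does not say what follows a missed survey.
- A reader might infer that VA data are barred from safety use, or that they are known to cover every participant. The article gives one purpose for them, does not call it the only one, and states neither coverage nor timing.
- A reader might infer that the trial claims walking is safe and so lacks the data to show it. The aims, outcomes and analysis contain no safety hypothesis or event-rate estimate, and the adverse event section itself allows that walking may become unsafe for some.
- A reader might take the 30% as the share who stop reporting events. It is an allowance for missing one-year outcome data. Someone who misses the 12-month survey may have answered earlier ones or telephoned, and someone who stays may skip surveys. It would be equally wrong to discard a lost participant's whole year when judging how precisely risk is known.

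Existing provisions also deserve credit: a toll-free line, a reporting link in every e-mail, upload tracking and medical clearance at entry.

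These objections limit the wording and the size, and all of them stand to that extent. They do not remove the core. The article gives adverse event monitoring its own section and lists the mechanisms; those used after entry all rely on participant report. That is a stated method that can be improved with data the study is already obtaining.

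**Conclusion.** The concern holds in a limited form. As described, ascertainment of adverse events rests on participant report, so serious events in those who disengage may be missed or under-counted. Roughly 60 to 78 of 260 participants may have incomplete self-report, using missing 12-month outcome data as a proxy. Under an assumed annual serious event risk of 2% to 10%, with half to all of the year uncovered, about 0.6 to 7.8 participants with an event would fall in that gap.

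The conclusion rests on three assumptions: that missing outcome data roughly tracks missing safety reports, that loss may be related to harm, and that no other event source exists in documents not shown. It does not show that events will go unseen. It touches neither the sample size nor the efficacy analysis. The point is a cheap improvement, not an error that invalidates the design.

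**What to change.** In Monitoring and Reporting of Adverse Events, name the VA medical record data as a second source of serious events: hospital admissions, emergency visits and deaths. Apply it to all randomised participants in both arms over the same 12 months, whether or not they upload or answer surveys. Report these events by arm as randomised, in a table separate from self-reported events, because the two sources differ in completeness. If such a review is already planned, one sentence saying so settles the point.

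The cost is slightly more extraction and one more table, with no added burden on participants. Extraction by arm is enough; a record check after every missed survey would be a much larger task and is not needed for this purpose.

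There are limits. Care outside VA is missed in both arms. A later extraction improves the count of events but does not by itself alert staff sooner. Before relying on this source, confirm that the extraction covers every randomised participant and includes these event types, and check the consent wording on record access.

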### Description of Measures and Data Collection Procedures

Measures have been selected to assess our principal hypothesis that the proposed intervention will increase walking, as measured by step counts, among intervention patients relative to controls and reduce pain-related functional interference. Potential mediating factors, such as self-efficacy, and the benefits of a walking program, such as improvements in mood and quality of life, are also of significant interest. Data collection includes a computer-based survey completed at baseline, 6 months and 12 months, a six-minute walk test conducted at baseline and 12 months, and the step counts collected when participants upload their pedometer data. We are also collecting quantitative information about patients' use of the system via computerized records that the system maintains of all contacts. Health services use is assessed by patient report and by data obtained from the VA computerized medical record system.

The primary outcome for this study is pain-related disability and functional interference. Following the recommendations made through the Initiative on Methods, Measurement, and Pain Assessment in Clinical Trials (IMMPACT) [64], we are using both a disease-specific measure, the Roland and Morris Back Pain Disability Questionnaire (RDQ) index, and a generic measure of pain-related functioning from the medical outcomes study [65]. We hypothesize that the intervention will decrease back pain-related disability and pain-related functional interference. The RDQ index is a 24-item scale that has been widely used in back pain studies as a measure of self-perceived disability. The scale has good internal consistency, discriminative validity and is sensitive to change [66-69]. The medical outcomes study (MOS) pain measurement instrument assesses the effect of pain on mood and behaviors as well as the severity of pain over the past 4 weeks [65]. There is limited information about how the MOS instrument compares with other pain assessments but it is easily understood by patients and produces scales that have relatively good internal consistency [65].

Secondary outcomes include average daily steps, functional status, general health-related quality of life and pain intensity. Walking, which is a key aspect of the intervention, is measured as the number of average daily steps using the Omron HJ-720ITC pedometer. Rather than having to rely on self-reported step counts, the Omron allows us to upload the objectively recorded pedometer data directly to a database through the use of an embedded USB port. All data are time stamped by the pedometer. As an objective measure of function and to help validate the step count data obtained using the study pedometers we are conducting a six minute walk test at baseline and 12 months [70,71]. Participants are instructed to walk as far as they can in six minutes without running or jogging, with the primary measurement being the distance covered during those six minutes. Patients' general physical and mental functioning is being measured using the SF-12^® ^Health Survey [72] and pain intensity is evaluated using a numeric rating scale with standardized anchors (0 = "no pain" and 10 = "worst pain imaginable"), as used in the VHA's Pain as the Fifth Vital Sign initiative [73]. Patients use this scale to rate their current level of pain and their average level of pain during the past four weeks.

Other secondary outcomes and potential moderators include pain-related fear or kinesiophobia, which is being measured using a revised version of the Tampa Scale of Kinesiophobia (TSK-R) [74]; self-efficacy for exercise, which is being measured using the Exercise Regularly Scale [75]; the presence of depressive symptoms, which is assessed using a ten-item version of the Center for Epidemiologic Studies Depression Scale (CES-D 10) [76]; and, socio-demographic characteristics, such as age, gender and education level, other health conditions (e.g., diabetes), body mass index, perceived social support, health services utilization and employment status. Finally, an administrative interface to the website and database allows the study staff to track participant progress as well as ascertain whether a participant has been uploading step count data. This database will be used to assess participants' use of the different intervention components. For example, we will know how often the participant uploads step counts, how often they log on to the website, and whether they participate in the e-community.

### Analysis Plan

The patient is the primary unit of analysis for this study. Our sample size calculation was based on the RDQ index as the primary endpoint with a minimally detectable effect size determined as a difference of 0.4 standard deviations (SD) based on published data [68,77,78]. To detect a difference of 0.4 SD with 80% power using a two-sided 0.05 level two-group t-test, we will enroll 130 subjects in each group, to allow for an attrition rate of 30% at one year and a sample with outcome data of 100 patients in each group.

To determine whether the intervention reduces pain-related functional interference we will compare the difference in the RDQ index at 12 months between the two groups using a linear mixed-effects model. Similarly, mixed-effects models will be used to assess the effect of the intervention on step counts, quality of life, pain intensity, pain related fear and self-efficacy for exercise. Identifying factors associated with a sustained increase in walking over a 12-month timeframe is an exploratory analysis within the intervention group.

In addition, to understand features of successful versus less successful intervention experiences, we will analyze data collected through our monitoring of participant system use and semi-structured interviews conducted with a purposeful sample of intervention participants (choosing a sample of eight who expressed high satisfaction with the intervention and/or improved walking and a sample of eight with poor satisfaction and/or outcomes). Using standard qualitative methods [79], we will identify central themes from these interviews associated with the success of the intervention.

The two major limitations of the study design are: (1) we will be unable to directly compare the effect of this intervention to the effects of other types of exercise programs that have demonstrated promise in randomized trials (e.g., Yoga); and (2) usual care patients will receive some intervention elements (e.g., they will receive a pedometer and some of the educational content). Nevertheless, we believe that the design represents the optimal compromise between scientific rigor and real-world practicality. Further, we expect that neither the pedometer nor the extra education will have a substantial influence on our primary outcome. If they do have any impact, the effect would be to reduce the likelihood of finding treatment differences between the control and intervention groups. Thus, the design for this study will provide rigorous evidence about the effectiveness of the proposed intervention, which is novel and has yet to be evaluated and determined to be effective in isolation, as well as information about possible implementation in other settings.

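### Enrolling 130 per group with 30% attrition leaves 91 per group with outcome data, not the stated 100, and 76.5% power for 0.4 SD on the stated t-test, not 80%

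*Protocol article*

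**What the plan says.** All the figures are in the first paragraph of the Analysis Plan in the protocol article.

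- Endpoint: "Our sample size calculation was based on the RDQ index as the primary endpoint".
- Operating characteristics: "To detect a difference of 0.4 SD with 80% power using a two-sided 0.05 level two-group t-test".
- Enrolment: "we will enroll 130 subjects in each group".
- Reason for that enrolment: "to allow for an attrition rate of 30% at one year and a sample with outcome data of 100 patients in each group".

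The next paragraph says that the 12-month RDQ will be compared between groups with a linear mixed-effects model. It does not say whether baseline RDQ enters that model, and neither paragraph gives a within-person correlation.

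**The concern.** The sentence gives the number enrolled, the proportion lost and the number remaining. Any two of these fix the third, and the three stated values do not agree. A loss of 30% applies to those enrolled, so the evaluable number should be divided by the retained share, 0.70. The stated 130 instead equals 100 × 1.30. That is consistent with the common slip of adding 30% of the target, although the article does not show the step.

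At stake is the power for the primary endpoint. If 100 per group with outcome data are needed for 80% power and the trial's own attrition assumption leaves fewer, the stated power and detectable difference do not follow. A reader also cannot tell whether the trial tolerates 30% or 23% attrition, or whether 91 or 100 per group are expected at 12 months.

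**Working it through.** **Inputs** (all from the Analysis Plan): difference d = 0.4 SD; two-sided α = 0.05; power 80%; two-group t-test with equal groups; 130 enrolled per group; 30% attrition at one year; 100 per group with outcome data.

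**Step 1: the evaluable target.** Normal approximation:

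n per group = 2 (1.960 + 0.842)² / 0.4² = 2 × 7.85 / 0.16 ≈ 98.1, rounded up to 99.

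The exact noncentral t calculation gives 99.08, so 100. The stated 100 reproduces. A one-sided test would need 78, so the stated two-sided basis is the one that was used.

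**Step 2: the attrition allowance.**

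- Remaining from 130: 130 × (1 − 0.30) = 91.
- Enrolment that leaves 100: 100 / (1 − 0.30) = 142.9, so 143 (check: 143 × 0.70 = 100.1).
- Attrition at which 130 leaves 100: 1 − 100/130 = 23.1%.
- Only the multiplied form returns the stated enrolment: 100 × 1.30 = 130.

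The gap is 9 per group, 9% of the stated evaluable sample, so rounding does not explain it.

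**Step 3: power at the number that remains.** Normal approximation: power = Φ(d√(n/2) − 1.960). For n = 91, 0.4 × √45.5 − 1.960 = 2.698 − 1.960 = 0.738, and Φ(0.738) = 0.770. With the exact values alongside:

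| With outcome data per group | Power for 0.4 SD, normal | Power for 0.4 SD, t-test | Difference detectable with 80% power, t-test |
|---|---|---|---|
| 100 (stated) | 80.7% | 80.4% | 0.398 SD |
| 91 (implied by 30% attrition) | 77.0% | 76.5% | 0.418 SD |

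The risk of missing a true difference of 0.4 SD is therefore 100 − 76.5 = 23.5%, against the planned 20%.

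**Step 4: could the planned model make up the loss?** The article gives no baseline-to-12-month correlation r for the RDQ, so r is an assumption here. If the model adjusts for baseline, the effective standardised difference is about 0.4 / √(1 − r²). At 91 per group, power is then:

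| Assumed r | Power |
|---|---|
| 0.2 | 78.2% |
| 0.3 | 80.3% |
| 0.5 | 87.3% |

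The break-even value is about r = 0.29.

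**The case against.** The strongest reply is that the trial will not be analysed with a t-test. The RDQ is collected at baseline, 6 and 12 months, and the primary comparison uses a linear mixed-effects model. If baseline RDQ enters that model, a correlation of about 0.29 or more would bring power back to 80% with 91 per group. This stands as a caution: it cannot be said that the final analysis will be underpowered, only that the stated calculation does not support its stated power. It does not rescue the sentence. The article ties its 80% explicitly to a t-test, claims no gain from adjustment and gives no correlation. No choice of model makes 130 × 0.70 equal 100.

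A second reply is that the loss is small: 3.5 points below the stated 80% power, and 0.418 instead of 0.40 SD. That is fair. No endpoint, test or estimand changes, and the full loss occurs only if attrition reaches 30%. But the 30% is the plan's own assumption, and the target of 100 has almost no slack.

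A third point is that the cause is inferred. A misstated attrition rate, with about 23% intended, would also give 130 and 100. That stands, and it is why the fix below offers two wordings.

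The fact that a journal article condenses a protocol is no answer. The inputs and the result are all printed, and they contradict each other.

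**Conclusion.** The sentence is wrong as written. The evaluable target of 100 per group is right for 0.4 SD, 80% power and a two-sided 5% t-test, but 130 enrolled per group does not reach it at 30% attrition. The expected number with outcome data is 91 per group, 9 short. On the stated t-test, power for 0.4 SD is 76.5%, and 80% power is available only for 0.418 SD or more.

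This rests on the plan's own figures, with attrition equal in both groups and the t-test applied to participants with outcome data. Power under the mixed model may be higher, but the article gives nothing from which to calculate it. Nothing elsewhere in the article reconciles the three numbers.

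**What to change.** Keep 130 per group and correct the sentence in the Analysis Plan in one of two ways, according to which figure was intended:

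- If 30% attrition is the planning assumption: *With 130 enrolled per group and 30% attrition at one year, 91 per group are expected to have outcome data, giving 76.5% power for 0.4 SD (80% power for 0.42 SD) with a two-sided 0.05 level t-test.*
- If 100 with outcome data is the planning target: *Enrolling 130 per group allows for 23% attrition at one year while retaining 100 per group with outcome data.*

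Either is a change of wording only and needs no extra participants. The cost is a slightly less favourable statement of power or of tolerated attrition. Keeping both 30% and 100 would instead require 143 per group, that is 13 more per group and 26 more in total (286 instead of 260).

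Restating the power for a baseline-adjusted model is not a substitute unless the assumed correlation is given and justified. It reaches 80% at 91 per group only if that correlation is about 0.29 or more.
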